### Main objective

Compare the number of hospitalizations due to anaemia of patients receiving monthly capillary Hb measurements and those receiving standard venipuncture monitoring.

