#### Sample size

The sample size was calculated at 138 patients, 69 in both the control and intervention group, thus making it possible to detect a difference in hospitalization of 25% (60% in the control group and 35% in the intervention group, based on the disposable information in the database of the health provider). This sample size also takes into account an alpha risk of 0.05, a beta risk below 20% and a 10% dropout rate, with bilateral comparison. The arcsin approach was used for this calculation.

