### Intervention

The Hb levels of participants in the intervention group will be taken once a month with a Veri Q® haemoglobinometer, that showed good performance data, in accuracy test compared with the reference value from Nihon Kohden MEK-6420 (R2 = 0.9881) and with the Sysmax reference value (R2 = 0.9968) [21]. If a patient’s haemoglobin level falls below their reference value, the nurse case manager will activate the transfusion circuit by scheduling an urgent referral to the day hospital, an outpatient service where short-term treatment and diagnostic tests are performed. The interdisciplinary team at this unit will prescribe and administer the transfusion and handle the hospital discharge, in a specific circuit between health levels created to this intervention.

The WHOQOL-BREF questionnaire on quality of life will be administered at the first visit and six and 12 months.

To know the satisfaction with the intervention, a single item survey will be administered upon inclusion in the study and six and 12 months. The question is “to what extent are you satisfied with your anemia control”, and the possible answers are not satisfied, satisfied and very satisfied.

An ad hoc satisfaction survey on the intervention will be administered upon inclusion in the study and six and 12 months.

Participants in the control group received standard monitoring, the frequency of which is variable, since it is determined by clinical criteria. The data will be collected by reviewing patients’ computerized clinical records and a bimonthly phone call to determine how many times they have been hospitalized and visited the A&E during the study period. The WHOQOL-BREF questionnaire on quality of life will be administered at the first visit and six and 12 months of inclusion in the study. Data will also be collected for the control group.

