### Expected results

#### The main result variables are

Number of hospitalizations due to anaemia.Number of A&E visits due to anaemia.Time elapsed between Hb measurement and circuit activation.Time elapsed between Hb measurement and when the transfusion is performed.Time elapsed between Hb measurement and return home.

The specific measurement variable is the Hb level taken with the Veri-Q® haemoglobinometer once a month.

Other variables are:Satisfaction with monthly anaemia monitoring: taken at six and 12 months. Ad hoc questionnaire.Quality of life: measured at the start of the study and six and 12 months. WHOQOL-BREF questionnaire [22, 23].Prescribed medication that might alter Hb or haematocrit levels.Signs and symptoms of anaemia at monthly visits (dyspnoea, asthenia, palpitations, bleeding, and chest pain).

Socio-demographic and clinical data will be collected from both groups for comparison, including age, sex, educational level, type of anaemia, primary care centre, the physician responsible for monitoring anaemia, cognitive status, inclusion in the case management program, number of haemogram controls performed via venipuncture.

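### Earlier transfusions and anaemia admissions are neither named as baseline data nor secured as covariates, so low-cost precision may be lost

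*Protocol article*

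**What the plan says.** The Main objective is to "Compare the number of hospitalizations due to anaemia of patients receiving monthly capillary Hb measurements and those receiving standard venipuncture monitoring". The outcome is therefore a count per patient.

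Under Expected results, the article states: "Socio-demographic and clinical data will be collected from both groups for comparison, including age, sex, educational level, type of anaemia, primary care centre". It goes on to the physician responsible for the anaemia and ends with "cognitive status, inclusion in the case management program, number of haemogram controls performed via venipuncture". Earlier transfusions, anaemia admissions and A&E visits are not named there, or as covariates anywhere else. Quality of life, a secondary outcome, does have a measurement at study start.

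Statistical analysis plans two-group comparisons, then a multiple linear regression. Its covariates are those that differ significantly in the univariate step, plus demographic and clinical variables thought relevant. None is named.

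Two places show that the history is probably within reach. The inclusion criteria require at least two red-cell transfusions for chronic anaemia within a year, so transfusion history has to be checked at screening. The Intervention section collects control-group admissions and A&E visits from "computerized clinical records and a bimonthly phone call", although for the study period only.

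**The concern.** Patients who need repeated transfusions are likely to differ a good deal in how often they are admitted. The natural predictor of a patient's admissions in the coming year is the number in the year before, with the transfusion count as a second marker of severity. If neither is in the model, that between-patient variation stays in the error term.

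The stated covariate rule does not deal with this. Its first part can select only a variable that has been recorded, and then only if it passes a significance test. Its second part depends on later judgement.

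What is at stake is precision and protection against chance imbalance. The planned power is only just above 80%, and the Discussion names recruitment difficulty as a main limitation, so precision that needs no extra patients is worth having.

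**Working it through.** **1. The plan's own figure.** Inputs from Sample size: the planned proportions are "60% in the control group and 35% in the intervention group, based on the disposable information in the database of the health provider". For error rates and losses the section gives "an alpha risk of 0.05, a beta risk below 20% and a 10% dropout rate, with bilateral comparison". The method it names is the arcsine transformation.

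- h = 2·asin(√0.60) − 2·asin(√0.35) = 0.506
- n per arm = 2·((1.960 + 0.842)/h)² = 61.3, rounded up to 62
- 62/0.90 = 68.9, rounded up to 69 per arm, 138 in total

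This agrees with "The sample size was calculated at 138 patients, 69 in both the control and intervention group". Power with 62 evaluable per arm is Φ(0.506·√31 − 1.960) = 80.4%. This is an unadjusted calculation, and nothing below makes it wrong.

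**2. A count model consistent with 60% in controls (assumption).** Take gamma-Poisson counts with mean μ and frailty variance θ, so that P(at least one admission) = 1 − (1 + θμ)^(−1/θ). Both (θ = 0.5, μ = 1.162) and (θ = 1.0, μ = 1.5) give 60%. If a share k of patients keep the same frailty from the earlier year to follow-up, the correlation of the two counts is about k·θμ/(1 + θμ).

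- θ = 0.5, k = 0.4: 0.4 × 0.581/1.581 = 0.15
- θ = 1.0, k = 1: 1.5/2.5 = 0.60

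The simulated correlations at these two ends were 0.14 and 0.59. The article gives no such correlation, so this range is assumed.

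**3. Smaller effect: rate ratio 0.6, 62 per arm.** Negative binomial fits with and without log(1 + prior count), 300 trials per setting, gave standard-error ratios from 0.989 to 0.848. Squared, these are 0.978 and 0.719, a variance reduction of 2 to 28%. Power went from 63% to 65% at the low end and from 52% to 66% at the high end. With 300 trials, each power figure has a simulation error of about 3 points (√(0.5·0.5/300) = 0.029).

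The protocol's own linear regression, 3,000 trials per setting, gives much the same:

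| Correlation | Variance reduction | Power without / with adjustment |
|---|---|---|
| 0.14 | 1% | 59% / 60% |
| 0.36 | 9% | 59% / 63% |
| 0.41 | 13% | 54% / 60% |
| 0.59 | 27% | 54% / 67% |

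Using only the eligibility-year transfusion count, truncated at two or more, standard-error ratios of 0.981 to 0.921 give a 4 to 15% reduction.

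**4. Planned effect.** A rate ratio of 0.6 is weaker than the plan assumes. It leaves 1 − (1 + 0.5·0.697)^(−2) = 45% (θ = 0.5) or 1 − 1/1.9 = 47% (θ = 1.0) of intervention patients with an admission, not 35%. To reach 35%, the intervention mean must be 0.481 or 0.538, a rate ratio of 0.41 or 0.36. With SE² = [(1/μ₀ + θ) + (1/μ₁ + θ)]/62 for the log rate ratio:

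- θ = 0.5: SE = √(3.94/62) = 0.252; 0.883/0.252 = 3.50; power 94%
- θ = 1.0: SE = √(4.52/62) = 0.270; 1.024/0.270 = 3.79; power 97%

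At these ratios the linear model with adjustment still cuts the variance by 1 to 23%, but power is already near its ceiling and rises only about 0 to 3 points.

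**5. A cruder check.** Applying the factor 1 − ρ² to the binary comparison in step 1 would lift 80.4% to 82.0% (ρ = 0.2) and 94.1% (ρ = 0.6). I put less weight on this. It is a linear-model approximation, and it starts from the power of a comparison of proportions rather than of counts.

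**6. Chance imbalance.** For a yes/no history variable with prevalence 30 to 60% and 69 per arm, the SD of the between-arm difference is √(2p(1 − p)/69), about 8 points. The chance of a gap above 10 points is about 20 to 24%.

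**The case against.** The strongest reply is that nothing in the text is wrong. The list of baseline data is introduced as a set of examples, the model admits further clinical variables considered relevant, and the article condenses a full protocol (version 6.0) in which the history may well be named. This stands against two stronger readings that a reader might infer. One is that the trial cannot adjust for earlier admissions. The article does not support that: the list is open, and history that predates randomisation can be extracted later. The other is that the data come at no cost. That is not shown either: record review is described for the study period, in the control-group paragraph, and eligibility needs only confirmation of two transfusions in a year, not an exact count for the year before randomisation.

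It is also fair to object that large power gains appear only for an effect smaller than planned, and that the 80.4% belongs to a comparison of proportions while the simulated gains belong to counts. Both objections stand and limit the size claimed.

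They do not remove the point. The article does state a covariate rule, and that rule leaves the most natural predictor of the main outcome to a significance test or to later judgement.

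**Conclusion.** The point holds as a worthwhile improvement, not as an error that threatens validity. The article neither names earlier transfusions, anaemia admissions and A&E visits as baseline data nor secures adjustment for them. A reader might infer that the treatment comparison is biased or that the trial is undersized. Neither follows: allocation is randomised, and 138 reproduces exactly.

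The size is a variance reduction of roughly 1 to 28% for assumed correlations of about 0.14 to 0.59. In power, that is about 0 to 3 points at the planned effect and up to about 14 points at a rate ratio of 0.6. All of this rests on the gamma-Poisson model, 62 evaluable patients per arm and a correlation that the article does not give. At the low end the gain is negligible.

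**What to change.** For both arms, extract from the clinical records the number of transfusions, anaemia hospitalizations and anaemia A&E visits in the 12 months before randomisation, with the same definition of an anaemia-related event as at follow-up. Name these counts among the baseline data. Pre-specify prior anaemia hospitalizations and prior transfusions as covariates in the main hospitalization model, and prior A&E visits in the A&E model, whatever their p-value.

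The cost is a few retrospective record fields per patient and a sentence in the analysis section. No visits are added. Patients already enrolled can be included, because the values predate randomisation and the allocation cannot have affected them. Before adopting this, confirm that the records identify earlier admissions as due to anaemia and can be reviewed for that period in both arms. If the full protocol already names these variables, only the covariate sentence is needed.

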## Discussion

Primary care professionals experience difficulties in monitoring haemoglobin levels in patients with chronic anaemia due to delays in receiving haemogram results, sometimes of up to 12 h. Using a haemoglobinometer in patients with chronic diseases and chronic anaemia would allow healthcare providers to detect the need for transfusions or other treatment and activate the hospital circuit at the corresponding care level early and quickly, thus preventing decreased quality of life and worse prognosis in patients, reducing decompensations and optimizing health resources.

The haemoglobinometer is a portable, pocket-sized device that can be easily transported to patients’ home. It is very simple to use and can be operated by any health professional with minimal training [14–16] . The technique consists of pricking the patient’s finger, collecting a drop of capillary blood with a micropipette and depositing it on a test strip inserted into the device [24]. In short, it is a simple technique that requires minimal training and can be performed in a matter of minutes.

Moreover, in our setting there is no existing a specific and direct circuit to introduce patients who were detected anemia in primary care, the intervention test a procedure to avoid this difficulty and try to improve the defragmentation of the health system for these patients, nor have we seen evidence of such a circuit in other regions with similar a population.

Therefore, this study will allow us to implement and assess a transfusion circuit, the rapid response of hospital resources to perform transfusions, user satisfaction with this resource, any incidents that may arise and any improvements needed. The results of this study are expected to facilitate the implementation of an early-detection anaemia circuit and a quick inter-level response that improves care for patients with chronic anaemia. Disseminating the protocol will facilitate reproducibility in other regions.

The figure of the nurse case manager is essential to carrying out the treatment circuit since they are responsible for defragmenting the health system [17–19]. That is why they are in charge of initiating and monitoring the entire intervention process in this study and employing fluid communication with all the parties involved.

Early detection of anaemia contributes to improved quality of life in patients with the clinical profile outlines in this study since we expect to find greater satisfaction among those who are monitored with a haemoglobinometer than those who undergo venipuncture. This expectation is based on the easier and less invasive technique used to obtain the sample [16], as well as lower levels of emotional distress, anxiety and uncertainty that patients experience while waiting for results that will determine what interventions will be necessary since, with a haemoglobinometer, the results are available almost immediately upon taking the sample. Moreover, by monitoring anaemia with a haemoglobinometer, we predict a drop in A&E visits and hospitalizations, thus reducing patients’ discomfort and the risks associated with such visits, as well as the health expense they represent.

One of the main limitations of this study is recruitment difficulty. In recent years, there has been a tendency to limit transfusions, meaning it is possible that fewer patients than initially expected meet the inclusion criteria. If the recruitment objectives cannot be met, the recruitment region could be expanded to include other nearby geographical areas with similar socio-demographic and health characteristics.

If the results of the study are as expected, health institutions could evaluate the possibility of using a haemoglobinometer to monitor patients who frequently experience anaemia and adding a transfusion circuit to the reference day hospital. If the hypothesis is confirmed, the number of hospitalizations and A&E visits would be reduced and patients’ quality of life would improve. Future studies might also hypothesize that healthcare costs would decrease considerably as well. The regular use of a haemoglobinometer by nurse case managers in primary and home care would enable early detection and treatment of anaemia.

### Trial status

Protocol version number: 6.0, date: 1 September 2017. Date the recruitment began: 6 March 2018. The approximate date when recruitment will be completed: 31st December 2023.

## Data Availability

Only the Prinicipal Investigator and the clinical trial supervisor have access to the data. The results will be disseminated via peer reviewed publication and conference presentation. This protocol is written according to the SPIRIT guideline.

## Abbreviations

Hb: Haemoglobin
HF: Heart failure
COPD: Obstructive pulmonary disease
A&E: Accident & emergency
